### Subclinical atherosclerosis imaging

#### **
*Carotid intima-media thickness (CIMT)*
**

At baseline and every year, CMIT are to be assessed in all subjects with an ultrasound system (IU22 Philips). Ultrasound images are acquired by linear high frequency 2-dimensional probes following the protocol of the Bioimage Study [28]. Carotid plaque is defined as a focal structure that protrudes into the lumen of the carotid artery at least 0.5 mm or ≥50% thicker than the surrounding. Three measurements each are made on the far wall of the left and right common carotid arteries in end diastole, 1 cm below the point of bifurcation. The average of the 6 readings will be taken as the CIMT value.

#### **
*Magnetic resonance imaging (MRI)*
**

At baseline and after the 5-year follow up, all subjects are to undergo a cerebral MRI. We use a multisequence MRI protocol on a 1.5-T scanner (GE Healthcare). For cerebral microbleeds detection we will use an accelerated three-dimensional T2*-weighted gradient-recalled echo sequence. MRI scans are viewed by radiology physicians blinded to the OSA status of the subject. As previously described cerebral microbleeds are defined as focal areas of very low signal intensity on T2*-weighted imaging without signal abnormalities on other structural sequences [29]. Microbleeds are classified according to cerebral localization (lobar brain sites or infratentorial locations).

### Power considerations

The calculation of EPIOSA’s planned sample size of 300 patients and 50 matched controls, is based on three estimations: a) in pediatric patients, those with OSA (n = 37), showed a reduced Treg population and altered Th1:Th2 balance toward Th1 predominance compared with non-OSA controls (n = 13) [30]; b) differences among DNA methylation in inflammatory genes were observed among OSA patients with high hsCRP (n = 31), compared with normal non-OSA controls (n = 31) [16]; and C) a randomized study showed that effective treatment of OSA with continuous positive airway pressure for 4 months significantly decreases IMT as early signs of atherosclerosis in 24 patients with severe OSA [31]. We expected a loss to follow-up of an average of 2% per year. In this way at the end of the 5-year follow-up we hope to analyze outcomes in 270 patients with OSA and 45 without OSA. This sample size ensures to analyze subgroups of patients according with prescribed treatment for OSA. Specifically, the sample will have 80% power to detect average IMT differences when comparing OSA patient treated and non-treated CPAP. The power is calculated based on a 2 SD with a significance level of 0.0125.

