### Statistical analyses

Groupwise comparisons (n >2) will be performed using a nonparametric Kruskal-Wallis test followed by a Mann–Whitney U test as appropriate. Pairwise comparisons were performed using a nonparametric Mann–Whitney test unless otherwise indicated. Chi square tests will be performed for categorical variables. Regression models will be applied to assess the effect of OSA, biomarkers, peripheral lymphocytes and epigenetic changes on CIMT, carotid plaque and cerebral microbleeds. All models will be adjusted for age and BMI, and additionally for covariables that may change the estimated risk beyond 5% Specific statistics procedures will be performed for the arrays as described above. STATA-12 for Windows (STATA CORP, TX, USA) are to be used for all analyses.

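### The stated 80% power for the CPAP comparison of IMT cannot be reproduced from a 2 SD input, a 0.0125 level and 270 OSA patients

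*Protocol article*

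**What the plan says.** The Power considerations section of the protocol article sets out a "planned sample size of 300 patients and 50 matched controls". It lists three earlier findings as the basis: a paediatric comparison of T-cell populations (37 versus 13), a comparison of methylation in inflammatory genes (31 versus 31), and a randomized CPAP study in 24 patients with severe OSA in which IMT fell over 4 months. As reported in the article, these give group sizes and directions of effect. They give no IMT difference, no SD and no expected proportion treated.

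On attrition it says "We expected a loss to follow-up of an average of 2% per year", and from this that "we hope to analyze outcomes in 270 patients with OSA and 45 without OSA".

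The one quantitative power claim follows: "Specifically, the sample will have 80% power to detect average IMT differences when comparing OSA patient treated and non-treated CPAP". Its basis is the single sentence "The power is calculated based on a 2 SD with a significance level of 0.0125". Sidedness is not stated, and no reason is given for 0.0125.

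The Study design section describes a non-interventional cohort in which CPAP is started according to national guidelines, so the investigators do not set the treated/untreated split. The Statistical analyses section plans Mann-Whitney tests for pairwise comparisons and regression models, adjusted for age and BMI, for carotid IMT. It states no significance level for them.

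**The concern.** A power statement needs a difference, a measure of spread, a level, group sizes and the resulting power, and these must agree. Here the article gives a power (80%), a level (0.0125), a total (270) and an ambiguous term (2 SD). On its most natural reading, as a standardized difference, 2 SD is so large that a handful of patients would detect it, and a study of 270 would not have a power as low as 80%. On the other readings the difference is absent.

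What is at stake is the interpretation of the CPAP comparison. The effect of CPAP on disease progression is the fifth specific aim, and the Discussion hopes to show a benefit on progression of subclinical atherosclerosis. If that comparison is null, a reader will look to the power statement to see which effects have been made unlikely. As written, it cannot tell them. Someone who takes only the 80% from it may assume that moderate effects were covered, when this depends on a split and a difference that the article does not give.

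**Working it through.** **Inputs from the article (Power considerations).** Power 80%; level 0.0125; 2 SD; 300 OSA patients and 50 controls enrolled; 2% loss per year for 5 years.

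**Assumptions, because the article is silent.** Two-sided test; an unadjusted comparison of two means at year 5; treated/untreated splits of 135/135, 189/81, 216/54 and 243/27.

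**Step 1: the analysed numbers.** A loss of 5 × 2% = 10% gives 300 × 0.90 = 270 and 50 × 0.90 = 45. Compounded, 0.98⁵ = 0.904 gives 271 and 45. This part of the section reproduces. Only the 270 OSA patients enter the CPAP comparison.

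**Step 2: the plan's power, with 2 SD read as the difference.** The normal quantiles are z(1 − 0.0125/2) = 2.498 and z(0.80) = 0.842, which sum to 3.339.

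- Normal approximation: n per group = 2 × (3.339/2)² = 5.6, so 6 per group.
- Noncentral t: 77% power with 7 per group and 85% with 8. So 8 per group, 16 in all, is the smallest equal-group design that reaches 80%.
- Allowing for the Mann-Whitney test with a relative efficiency of 0.955 or 0.864 gives 8 or 9 per group. A one-sided test would need 7 per group (t).

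With 270 patients, the standardized shift is 2/√(1/n₁ + 1/n₂). At 135/135 it is 2/0.1217 = 16.4; at 243/27 it is 2/0.2029 = 9.9. Against a critical value of about 2.5, power is above 99.9% at every split from 1:1 to 9:1. It comes down to about 80% only when one group almost vanishes: 266 versus 4 gives 93% and 267 versus 3 gives 82%.

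**Step 3: the other readings.** If 2 SD means a standard deviation of 2 in some unit, or is a slip for two-sided, the sentence contains no difference. Power is a function of the difference, so 80% is then undefined and nothing can be checked.

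No reading gives 80% from the stated inputs at a realistic split.

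**Step 4: what 270 patients could detect (illustration only).** The detectable difference in SD units at 80% power is 3.339 × √(1/n₁ + 1/n₂). Power for a 0.3 SD difference is from the noncentral t.

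| Assumed split | √(1/n₁ + 1/n₂) | Detectable at 80% power | Power for 0.3 SD |
|---|---|---|---|
| 135/135 | 0.1217 | 0.41 SD | 48% |
| 189/81 | 0.1328 | 0.44 SD | 40% |
| 216/54 | 0.1521 | 0.51 SD | 30% |
| 243/27 | 0.2029 | 0.68 SD | 15% |

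A Mann-Whitney test with efficiency 0.955 raises the detectable difference by about 2% (1/√0.955 = 1.023), for example from 0.41 to 0.42 SD at 135/135. At a two-sided level of 0.05 the figures would be 0.34 SD (135/135) and 0.43 SD (216/54).

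**The case against.** The strongest reply is that the article says only "The power is calculated based on a 2 SD" and never calls this a difference. The 16-patient result therefore belongs to one reading, and the fair criticism is that the sentence is unclear. That is right about the wording, but it does not rescue the claim: the alternative readings leave the 80% without a difference to attach to.

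A second reply is that a journal article condenses a fuller calculation, and that the three cited studies, which are not at hand, may supply an IMT difference and an SD. That stands as far as it goes; it cannot be said that no proper calculation exists. But the article chose to print a power together with its inputs, and those do not agree. This is more than a detail left to another document.

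Several stronger inferences are tempting and should not be drawn:

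- **That the study is underpowered.** Read as a 2 SD difference, power is far above 80%, and a restated figure near 0.4 to 0.7 SD would look more favourable than 2 SD. Nor is power low for everything below 2 SD: for 1 SD it is still about 99% at 243/27. It falls below 80% only under the detectable differences in the table.
- **That 0.41 to 0.51 SD is the study's true detectable difference.** The article gives no split or sidedness, IMT is measured yearly, and adjusted regression is planned. The table is an illustration.
- **That planning and testing use different levels.** The Statistical analyses section gives no level for these tests, so nothing there conflicts with 0.0125. Reading 0.0125 as 0.05/4 for four contrasts is also an inference; the article gives no reason for it.

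**Conclusion.** The point holds as a failure of the power statement to reproduce. With 2 SD as the difference and a two-sided 0.0125 level, 16 patients are enough and 270 give almost 100% power; with 2 SD as anything else, the 80% has no meaning. Neither conclusion depends on the assumed split, short of a group of about three patients. The attrition arithmetic is correct.

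The detectable differences of 0.41 to 0.68 SD, and the power of 48% down to 15% for 0.3 SD, do depend on the assumed splits, a two-sided test and an unadjusted comparison of all 270 OSA patients. They show the scale of what the sentence leaves out. They are not a finding that the sample is too small. The consequence is interpretive: as written, the article does not tell a reader which CPAP effects a null result would make unlikely.

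**What to change.** Replace the sentence on 2 SD with a detectable-difference statement that gives the IMT difference (in mm or SD units), its SD and source, the sidedness, the expected numbers treated and untreated at year 5, and the resulting power. If the split cannot be predicted, give the detectable difference over a range of splits, as in the table above, and label the splits as assumptions. The authors should first establish what 2 SD was meant to be, so that one uncheckable statement is not replaced by another.

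In the same place, say which comparisons the 0.0125 level covers, so that the level used for planning is also the one used for testing.

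The cost is wording only. No patients, visits or measurements change.

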### Statistical analyses

Groupwise comparisons (n >2) will be performed using a nonparametric Kruskal-Wallis test followed by a Mann–Whitney U test as appropriate. Pairwise comparisons were performed using a nonparametric Mann–Whitney test unless otherwise indicated. Chi square tests will be performed for categorical variables. Regression models will be applied to assess the effect of OSA, biomarkers, peripheral lymphocytes and epigenetic changes on CIMT, carotid plaque and cerebral microbleeds. All models will be adjusted for age and BMI, and additionally for covariables that may change the estimated risk beyond 5% Specific statistics procedures will be performed for the arrays as described above. STATA-12 for Windows (STATA CORP, TX, USA) are to be used for all analyses.

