## Methods/Design

### Study objective

The EPIOSA study has the following specific aims: 1) Use of questionnaires, sleep studies, carotid ultrasonography and cerebral magnetic resonance imaging (MRI) for the definition of OSA subpopulations and controls among individuals without comorbidities; 2) Identification and definition of the parameters that predict disease progression over 5 yrs of follow-up. For the purposes of the present study, disease progression is defined in terms of changes in sleep disordered breathing variables, symptoms, carotid artery intima-media thickness (IMT) and plaque and new microblebs in MRI; 3) Identification of useful biomarkers for disease progression by measuring known biomarkers that correlate with OSA severity, in blood and urine samples; 4) Identification of novel epigenetic factors and/or biomarkers correlating with poor outcomes in OSA and controls. This will be analyzed by cytometry analysis, DNA methylation in genes subserving inflammatory functions RNA transcriptomics; and 5) assessment of the effect of CPAP (Continuous positive airway pressure) on inflammatory and epigenetic mechanisms and disease progression.

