At baseline and every year, whole blood samples are drawn using a 21G butterfly needle into serum gel, EDTA, sodium fluoride and PaxgeneW tubes (PreAnalytix GmbH, Switzerland). Serum glucose, triglycerides, total cholesterol and HDL cholesterol will be measured by spectrophotometry (Chemical Analyzer ILAB 650, Instrumentation Laboratory), and serum apolipoproteins A and B, will be measured by kinetic nephelometry (Immunochemistry Analyzer IMMAGE 800, BeckmanCoulter). Within two hours after collection, high sensitive C-reactive protein (CRP) will be measured based on a particle-enhanced turbidimetric immunoassay technique. For biobanking, about 15 ml of EDTA blood and 5 ml of blood without anticoagulant for serum preparation are to be fractionated into plasma, serum and whole blood and in 1 ml dot-coded metal-free cryotubes are to be stored at -80°C. Inflammatory markers to be assessed are shown in Table 2.

**Table 2 T2:** Outcome measurements in the Epigenetics in Obstructive Sleep Apnea (EPIOSA) study

**Measurement**	**Description**	**Frequency of assessment**
Questionnaires, Dietary, Epworth Sleepiness Scale		Each visit
Vital signs	Including sitting blood pressure, heart rate, height and weight	Each visit
Exhaled carbon monoxide	Confirmation of smoking status	Each visit
Spirometry	Post-bronchodilator FVC, FEV1 and FEV1/FVC	Baseline
Electrocardiogram	12-lead resting electrocardiogram	Baseline
Sleep Study	At home type 3 monitor for diagnosis and at home autoCPAP for CPAP titration (if appropriated)	Baseline and every year
Blood sample	Standard biochemistry and lipid markers: Total cholesterol, LDL, HDL, TG, Apo A, Apo B.	Baseline and last visit
	Inflammatory markers: TNF-α, IFN-ϒ, IL-1β, IL-6, IL-8, IL-10.	
Urine sample	Microalbuminuria, 8-isoprostane	Baseline and every year
Carotid Ultrasonography	High-resolution B-mode assessment of carotid artery intima-media thickness and plaque	Baseline and every year
Magnetic resonance imaging	Cerebral microbleeds detection	Baseline and last visit
Flow cytometry	Fresh peripheral blood T-cell phenotype	Baseline and last visit
DNA methylation	Genome-wide DNA methylation status	Baseline and last visit
miRNA microarray analysis	Levels of candidate miRNAs regulated by aberrant DNA methylation	Baseline and last visit

#### **
*Flow cytometry*
**

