Part of the blood samples collected in EDTA tubes are stored at -80°C until DNA isolation, which is performed in the Department of Molecular Biology at the Faculty of Veterinary of the University of Zaragoza. Genomic DNA is obtained with the use of the illustra blood genomic Prep Midi Flow Kit (GE Healthcare, UK) following the manufacturer’s instructions. Genome-wide DNA methylation profiles will be studied in approximately 1 μg of genomic DNA treated with sodium bisulfite. The converted DNA will be analyzed using Illumina’s Infinium Human Methylation 450 BeadChip assay (Illumina, San Diego, CA, USA). To minimize position effects, cases and controls will be randomly distributed. The assay allows determination of DNA methylation levels at >450,000 CpG sites covering all designable RefSeq genes, including promoter, 5′, and 3′ regions. It captures CpG islands and shores, non-CpG methylated sites, microRNA promoter regions and disease-associated regions identified through genome-wide association studies [24]. Illumina array data will be processed using the Methylation Module of GenomeStudio v1.9 software. To identify differentially methylated regions (DMRs), we will use a 1-kb sliding window and apply Fisher’s method to combine P values for each 1-kb region on the basis of all probes within each window [25]. Significant DMRs will be selected at a 1% FDR on autosomes and 5% FDR on chrX. After statistical analyses, the methylation patterns of the gene of interest will be confirmed by sequencing of the 24 bisulfite-treated DNA samples used for the genome wide analysis.

#### **
*Gene expression analysis*
**

Blood samples stored at -80°C in PaxGene (TM) tubes will be used for total RNA isolation using PAXgene Blood RNA Kit (Qiagen, Venlo, Netherlands). Quantitative real time polymerase chain reactions (qRT-PCR) will be performed to test whether differential methylation patterns of the selected genes affect their expression level. Complementary DNA will be synthesized from total RNA using random hexamers and the SuperScript^®^ III First Strand Synthesis Kit (Life Technologies, Carlsbad, California, US). Primers and TaqMan^®^ probes will be selected from the Applied Biosystems Inventories Assays and qRT-PCR will be performed in a The StepOne™ Real-Time PCR System (Applied Biosystems, Life Technologies, Carlsbad, California, US).

#### **
*MicroRNA analysis*
**

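### Aim 5 has no adjusted analysis of the CPAP effect on serum inflammatory markers and T-cell subsets: the only stated two-group method is an unpaired Mann-Whitney test without covariates, although CPAP is not randomised

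*Protocol article*

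**What the plan says.** All references are to the protocol article, Methods/Design.

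- **Study objective, aim 5:** "assessment of the effect of CPAP (Continuous positive airway pressure) on inflammatory and epigenetic mechanisms and disease progression". Markers are outcomes here and CPAP is the exposure.
- **Study design:** the study is non-interventional, and CPAP is started by the national guidelines.
- **Statistical analyses, default test:** "Pairwise comparisons were performed using a nonparametric Mann–Whitney test unless otherwise indicated".
- **Statistical analyses, models:** "Regression models will be applied to assess the effect of OSA, biomarkers, peripheral lymphocytes and epigenetic changes on CIMT, carotid plaque and cerebral microbleeds". The adjustment for age, BMI and covariables chosen on a 5% change in the estimate belongs to these models.
- **Statistical analyses, arrays:** "Specific statistics procedures will be performed for the arrays as described above". For methylation this points to DNA methylation analysis: 1-kb windows, Fisher-combined P values, and "Significant DMRs will be selected at a 1% FDR on autosomes and 5% FDR on chrX".
- **Laboratory analysis:** "At baseline and every year, whole blood samples are drawn". Table 2 lists the inflammatory markers in the blood-sample row, and for flow cytometry gives "Fresh peripheral blood T-cell phenotype Baseline and last visit".

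**The concern.** No stated model has a serum marker or a T-cell subset as its outcome. For these markers the treated versus untreated comparison is therefore left to the default test, which is unpaired and carries no covariates. It takes in neither baseline OSA severity nor, if run on last-visit values, the man's own starting level.

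In a randomised study this would cost only precision. Here CPAP follows a guideline, and aim 3 concerns markers that correlate with OSA severity, so the two groups may start at different marker levels. A baseline gap then enters the comparison as if it were a CPAP effect. The study could report that CPAP does or does not lower inflammation because of who was prescribed it. Blood for the baseline value is already collected, so the remedy needs no new data.

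**Working it through.** **1. Which method reaches which outcome**

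| Outcome in aim 5 | Stated method | Adjusted? |
|---|---|---|
| Serum inflammatory markers | Mann-Whitney default | No |
| T-cell subsets | Mann-Whitney default | No |
| Genome-wide methylation | Own array procedure with FDR selection | CPAP contrast not stated |
| miRNA | Own array processing (2^-∆∆Ct) | CPAP contrast not stated |
| CIMT, plaque, microbleeds | Regression | Age, BMI and others; CPAP not named as exposure |

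The first two rows are the subject here.

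**2. The plan's own figures.** Loss of 2% a year for 5 years gives 300 × 0.90 = 270 and 50 × 0.90 = 45, as Power considerations states (compounded: 300 × 0.98^5 = 271.2 and 50 × 0.98^5 = 45.2). The 80% power claim concerns IMT only. It cannot be reproduced, because neither the IMT difference nor the CPAP split is given.

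**3. Assumptions not in the documents.** The 270 OSA patients split 135/135. The marker is normal with SD 1. The baseline-to-last-visit correlation is ρ = 0.5 (range 0.3 to 0.7). Treated men are g = 0.3 SD higher at baseline. The two-sided level of 0.0125 is borrowed from the IMT power statement (z = 2.498). The standard error of a difference in means is √(1/135 + 1/135) = 0.1217 SD.

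**4. The gap regresses to ρ × g.**

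- Bias in last-visit values: ρg = 0.5 × 0.3 = +0.15 SD.
- Bias in raw changes: ρg − g = 0.15 − 0.30 = −0.15 SD. The SD of a change is √(2(1 − ρ)) = 1, so the standard error is the same.
- False positives with no CPAP effect: 0.15/0.1217 = 1.232, and Φ(1.232 − 2.498) ≈ 10% for a test on means. Simulated Mann-Whitney tests give about 9 to 10% for either version, against a nominal 1.25%. Regression on the baseline value stays near 1.3%.
- With a true effect of −0.40 SD, last-visit values estimate −0.40 + 0.15 = −0.25 (about 30% power), changes estimate −0.40 − 0.15 = −0.55, and baseline-adjusted regression estimates −0.40.
- With g = 0.5 SD, the biases are ±0.25 SD and false positives about 31%.

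**5. The gap persists in full.** Last-visit values are biased by g = +0.30 SD and raw changes by 0. Adjustment for baseline alone is biased by (1 − ρ)g = 0.5 × 0.3 = +0.15 SD. Neither changes nor baseline adjustment is therefore safe in both cases, and a measure of what produces the gap (baseline AHI) has to be in the model.

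**6. No gap: precision only.** An effect with 80% power unadjusted is (2.498 + 0.842) × 0.1217 = 0.406 SD. Adjustment multiplies the residual variance by 1 − ρ², so power is Φ(3.339/√(1 − ρ²) − 2.498):

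- ρ = 0.3: Φ(1.00) = 84%
- ρ = 0.5: Φ(1.36) = 91%
- ρ = 0.7: Φ(2.18) = just over 98%

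A 200/70 split gives the same powers for an effect of 0.46 SD.

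**7. What the AHI term costs.** If CPAP and AHI correlate at c, the variance of the CPAP coefficient rises by 1/(1 − c²) when AHI explains no further marker variance. At c = 0.6 this is 1/0.64 = 1.56. For −0.40 SD and ρ = 0.5, 0.40/(0.1217 × 0.866) = 3.79 gives Φ(1.30) = 90%. Dividing by √1.56 = 1.25 gives Φ(3.04 − 2.498) ≈ 70%.

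**The case against.** The article condenses a fuller plan, and Mann-Whitney is a general default with an escape clause, never expressly assigned to aim 5. That is fair as far as it goes. But the article does fix a default and does list the outcomes of its models, and nothing in it indicates another method for serum markers or T-cell subsets. The choice is stated and suits this aim poorly.

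Four stronger readings may tempt a reader, and the documents do not support them.

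- *The whole epigenetic part of aim 5 falls to Mann-Whitney.* It does not. The arrays have their own procedures, and gene-level methylation is confirmed in only 24 samples, where a regression on five terms would be barely estimable.
- *The plan ignores the baseline value.* The text does not exclude a test on within-man changes. What holds is that neither version adjusts for baseline level or severity.
- *Treated men start higher, so the bias has a known direction.* The Background cites studies with no independent association of OSA with IL-6 or CRP, and the Discussion calls the CRP results conflicting. A gap is plausible, not established.
- *Baseline adjustment by itself removes the bias.* That holds only if the gap regresses as in step 4. Step 5 shows the opposite case.

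It is also fair that the power figures in step 6 exclude AHI. If c is as large as ρ, the precision gain disappears, because 1 − ρ² and 1/(1 − c²) then cancel. The case for the AHI term rests on bias, not power.

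Finally, the Flow cytometry text mentions blood at baseline only, while Table 2 adds the last visit. The T-cell part relies on Table 2.

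**Conclusion.** The point holds for serum inflammatory markers and T-cell subsets. Aim 5 treats them as outcomes of a non-randomised treatment, and the only stated two-group method adjusts for nothing.

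The size depends on quantities that the documents do not give. With a 0.3 SD gap that half regresses, the bias is 0.15 SD, upward for last-visit values and downward for changes, with a false-positive rate of about 9 to 10% instead of 1.25%. With a gap that persists, last-visit values are biased by the full 0.3 SD, changes are unbiased, and baseline-only adjustment is off by 0.15 SD. With no gap, only precision is at stake. Adding AHI protects against the persistent gap to the extent that AHI accounts for it.

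A reader might infer that the disease-progression part of aim 5 is well served by comparison. CPAP is not named as an exposure in the CIMT, plaque and microbleed models either. Repairing those models would still leave no model with a marker as outcome. The change should be made, but it is not a fatal flaw.

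**What to change.** In Statistical analyses, add:

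> For each serum inflammatory marker and T-cell subset, the CPAP effect among OSA patients will be estimated by linear regression of the last-visit value (log-transformed where skewed) on CPAP group, baseline value of the same marker, baseline AHI, age and BMI. Mann-Whitney tests are descriptive.

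Leave genome-wide methylation and miRNA to their array procedures, and keep the 24-sample methylation confirmation outside this model. Align the Flow cytometry text with Table 2 on whether a last-visit sample is taken, since the T-cell model needs one.

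The cost is one sentence and a little analysis time, with no new samples, visits or patients beyond the Table 2 schedule. Men without a baseline assay drop out of that marker's model or need imputation, and collinearity between CPAP and AHI costs some precision (step 7).
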